## Methods: participants, interventions and outcomes

### Study setting {9}

Participant recruitment is based at two sites within the United States: The Department of Veterans Affairs (VA) Greater Los Angeles and the Atlanta VA, within the Geriatric Research, Education and Clinical Centers and respective outpatient clinics at each site. Additionally, patients are recruited from outpatient clinics at two universities affiliated with these VA centers, the University of California Los Angeles (UCLA) Health System and Emory University. Data coordination activities are based at the University of California, San Francisco (UCSF). Additional quality control for intervention (e.g., fidelity ratings) is conducted by co-investigators at the Birmingham VA and the University of Utah/Salt Lake City VA. This list of study sites is comprehensive and is also available from the corresponding author.

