## Assignment of interventions: allocation

### Sequence generation {16a}

A secure unpredictable allocation sequence (e.g., A B B B A) was generated using randomly permuted blocks, stratified by site and sex, to maximize balance between groups throughout accrual while ensuring the sequence remain unpredictable. The randomization scheme was generated by computer (SAS, SAS Institute Inc., Cary, North Carolina). To avoid manipulation of randomization, a statistical analyst who was not otherwise involved in development of the study database, data cleaning, or data analysis was contracted to program the randomization scheme.

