## Statistical methods

### Statistical methods for primary and secondary outcomes {20a}

#### Primary comparative analyses

Our primary analysis will assess the intention-to-treat (ITT) effect of the integrated behavioral therapy program (integrated nocturia and insomnia intervention program) on nocturia frequency compared to the health education group (the primary outcome is single item from ICIQ-OAB 4 months post-randomization). The ITT approach is the standard approach for intervention evaluations in a randomized trial and will include all the randomized participants, including dropouts and non-adherent participants, in the analyses to ensure valid group comparisons. (Generalized) linear mixed effects models (G)LMMs will use all available data from all the randomized participants based on less stringent assumption than completed case analyses. The analyses will adjust for the stratified randomization variables (study site and sex) as suggested in the statistical literature that failure to adjust variables used in the randomization process can result in large *P* values and wide confidence intervals [64]. We expect that the covariates (age, sex, race/ethnicity, education, socioeconomic status, and clinical measures [i.e., presence of nocturnal polyuria or obstructive sleep apnea]) will be balanced between the intervention and control groups at baseline by randomization. However, if by any chance, there are any baseline covariates imbalanced between the intervention and control groups, they will be included in the (G)LMM fixed effects to control for potential confounding.

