Aim 1/Hypothesis 1: *Compared to control, participants assigned to the integrated nocturia and insomnia behavioral intervention will demonstrate a greater reduction in nocturia frequency over 4 months*. The primary outcome of nocturia frequency will be measured as the average episodes per night at baseline, 1 week after intervention (approximately 2 months), and 4 months through the ICIQ-OAB questionnaire’s nocturia item. An LMM will be used to evaluate the group difference over time in average nocturia frequency per night, with group (the integrated intervention vs. control), time, time*group interaction, and stratified randomization variables (study site and sex) in fixed effects, and nested two-level random effects to account for correlations due to clustering by study site and participants. The time*group interaction will provide the estimated ITT effect of the integrated intervention on nocturia frequency over time. Imbalanced baseline variables, if any will be included in the LMM.

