#### Secondary comparative analyses

Aim 2/Hypothesis 2: *Compared to control, participants assigned to integrated nocturia and insomnia behavioral intervention will have greater reduction in self-reported wake after sleep onset and Insomnia Severity Index over the 4-month follow-up period*. Secondary outcomes, patient-reported wake after sleep onset and ISI, will be modeled similarly with a (G)LMM in the original scale or transformed scale as appropriate, where group, time, time*group interaction, and stratified randomization variables (study site and sex) will be included in fixed effects, and random effects will be included for nested clustering by site and participant to account for correlations due to clustering. If the distributions of the secondary outcomes are skewed and no good transformation is found, the outcomes will be categorized into categories based on quantiles or clinically meaningful values and then modeled with GLMMs using cumulative logit or generalized logit link for multinomial data. Similar fixed and random effects will be included in GLMMs. Due to the exploratory feature, no adjustment will be made for the multiple comparisons, but results will be presented as secondary outcome analyses. Secondary analyses similar to those proposed in Aim 1 will be performed on the secondary outcomes of patient-reported wake after sleep onset and ISI.

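### Study site is entered as both a fixed and a random effect with only two sites, and a participant random effect alone can misstate the 4-month standard error in either direction

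*Protocol article*

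**What the plan says.** For Aim 1 (protocol article, Primary comparative analyses) the linear mixed model contains group, time, "time*group interaction, and stratified randomization variables (study site and sex) in fixed effects", together with "nested two-level random effects to account for correlations due to clustering by study site and participants". The Secondary comparative analyses section repeats the structure for wake after sleep onset and the Insomnia Severity Index: "random effects will be included for nested clustering by site and participant to account for correlations due to clustering". The section on additional analyses {20b} carries similar fixed and random effects over to the nocturia quality-of-life and sleep-quality scores.

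On the number of sites: "Participant recruitment is based at two sites within the United States" (Study setting {9}). Site is also a randomization stratum, the sequence being "generated using randomly permuted blocks, stratified by site and sex" (Sequence generation {16a}).

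The primary outcome is measured three times, "at baseline, 1 week after intervention (approximately 2 months), and 4 months through the ICIQ-OAB questionnaire’s nocturia item". The effect is read from the interaction: "The time*group interaction will provide the estimated ITT effect of the integrated intervention on nocturia frequency over time". The target time is 4 months: "the primary outcome is single item from ICIQ-OAB 4 months post-randomization".

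The article does not say whether the participant effect is an intercept only, whether time is categorical or linear, or what residual covariance applies. It gives no variance or correlation for any visit.

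**The concern.** Two things in the model statement need attention.

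**Site.** A variance component for site has to be estimated from differences between sites. With two sites there is one such difference, and the fixed site term already uses it. The random site term therefore has no data behind it.

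**Visits.** A participant random intercept with independent residuals implies one variance for all visits and one correlation for every pair. The three visits are unlike each other: an untreated baseline selected at two or more episodes per night, a visit one week after treatment, and the 4-month visit. The primary test concerns change from baseline to 4 months, so its standard error depends on the covariance of that pair. The random-intercept model replaces it with an average over all three pairs. If the average differs from the truth for that pair, the nominal 5% level is not the actual level.

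**Working it through.** **The plan's own figure.** The Sample size section states more than 80% power for a difference of 0.7 episodes per night with 192 participants, two-sided 5% and under 15% loss. With 96 × 0.85 = 81.6 per arm and a two-sample comparison of means, power is 99.4%, 96.1%, 89.1% and 79.8% for SDs of 1.0, 1.2, 1.4 and 1.6. The article calls 0.7 more than half an SD, which implies an SD below 0.7 / 0.5 = 1.4, so the claim is reproduced. The section gives no correlations, so it does not show what covariance was intended.

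**Site variance.** Inputs: 192 participants, two sites, three visits, fixed effects as stated, participant and residual variances of 1 (assumed). The REML log-likelihood of one simulated data set was evaluated at four values of the site variance:

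| Site variance | REML log-likelihood | Group × 4-month estimate | Its SE | SE of site term |
|---|---|---|---|---|
| 0 | −426.60479 | −0.789 | 0.2041 | 0.17 |
| 0.1 | −426.60479 | −0.789 | 0.2041 | 0.48 |
| 1 | −426.60479 | −0.789 | 0.2041 | 1.42 |
| 10 | −426.60479 | −0.789 | 0.2041 | 4.48 |

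The likelihood is flat, so the variance is not identifiable. The treatment estimate and its SE do not move; only the SE of the site term does. In a second data set the SE of the intercept likewise ran from 0.15 to 3.2 over the same range.

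**Random intercept and the 4-month contrast.** Assumptions: categorical time, complete data, independent residuals. Write D(jk) = s_j² + s_k² − 2 r_jk s_j s_k for the variance of the difference between visits j and k, with 0, 2 and 4 for baseline, 2 and 4 months. The random-intercept model estimates twice the residual variance as the mean of D(02), D(04) and D(24). The true quantity is D(04). Hence

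- SE ratio (model / true) = √[ mean(D(02), D(04), D(24)) / D(04) ]
- actual type I error = 2 × [1 − Φ(1.96 × ratio)]

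Example, SDs 0.7/1.1/1.1 and correlations 0.40/0.35/0.75 (baseline–2 months, baseline–4 months, 2–4 months): D = 1.084, 1.161, 0.605; mean 0.950; ratio √(0.950 / 1.161) = 0.905; type I error 7.6%.

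| SDs at 0/2/4 months | Correlations 02/04/24 | Ratio | Type I error |
|---|---|---|---|
| equal | 0.50/0.50/0.50 | 1.000 | 5.0% |
| equal | 0.50/0.40/0.60 | 0.913 | 7.4% |
| equal | 0.40/0.35/0.70 | 0.892 | 8.1% |
| equal | AR(1), rho 0.5 | 0.882 | 8.4% |
| equal | AR(1), rho 0.8 | 0.839 | 10.0% |
| 0.7/1.1/1.1 | 0.40/0.35/0.75 | 0.905 | 7.6% |
| 0.7/1.1/1.1 | 0.40/0.35/0.60 | 0.960 | 6.0% |
| 0.7/1.1/1.1 | 0.40/0.40/0.55 | 1.001 | 5.0% |
| 0.7/1.1/1.1 | 0.50/0.50/0.50 | 1.049 | 4.0% |
| equal | 0.50/0.60/0.50 | 1.080 | 3.4% |
| 1/1.3/1 | 0.50/0.50/0.50 | 1.122 | 2.8% |

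Simulation agrees. With 82 per arm and 20,000 replicates, type I error was 7.7% for 0.7/1.1/1.1 with 0.40/0.35/0.75, 8.0% for equal SDs with 0.40/0.35/0.70, and 5.1% when equal variances and correlations hold. A smaller run (200 replicates, about 15% dropout, Monte Carlo error about 2 points) gave 5.5% under equal correlations and 11% under AR(1) with rho 0.7, against 9.5% from the formula.

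**The case against.** The site duplication does not touch the trial's answer. The primary inference is the time-by-group interaction, whose estimate and SE are the same at every site variance, and in practice software would report a zero or singular component that the analyst would drop. That is right as to consequence. A reader might infer that the double entry of site undermines the treatment comparison; the check shows that it does not. It remains a specification error in the primary and secondary models, and an analysis plan that follows the text would inherit it.

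On the visits, the article never says intercept only. A random slope or a residual covariance in an analysis plan not shown would be compatible with its wording, and a condensed article commonly leaves such detail to that plan. This also stands: silence about the covariance is not in itself a fault, and the point is conditional on the natural reading of random effects for clustering by participant.

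A reader might further infer that the 4-month SE must be too small and the primary test anti-conservative. The documents do not support that. They give no variances or correlations, and the direction depends on both. A smaller baseline SD, which the entry criterion could produce, pushes the ratio upward by itself. Nor does 5% require equal correlations: with SDs 0.7/1.1/1.1, correlations 0.40/0.40/0.55 give 5.0%, while equal correlations of 0.40 give 3.9%. What survives is that the nominal level holds only under particular covariance patterns, and that stronger correlation between the two post-treatment visits, which is plausible, is a pattern that inflates the error.

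**Conclusion.** The point holds in two parts of different strength.

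- **Unconditional:** with two sites, the random site term next to a fixed site term is not identifiable. The cost is a possible singular or non-converging fit, arbitrary SEs for the intercept and site terms, and a decision after the fact about which term to remove. The treatment effect and its SE are unaffected.
- **Conditional:** if the participant effect is a random intercept with independent residuals, the SE of the 4-month contrast can be wrong in either direction. Type I error is about 6–8.5% when the 2-to-4-month correlation clearly exceeds those with baseline, up to about 10% under AR(1), 5% under equal variances and correlations, and about 3–4% under some other patterns. Every SD and correlation behind these figures is an assumption, as are categorical time and, for the formula, complete data.

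Severity is moderate: worth correcting before the analysis, but not a demonstrated failure of the primary test.

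**What to change.** Keep site and sex as fixed effects only and delete the random site term from the primary, secondary and additional models, including the generalized models for categorized outcomes. For continuous outcomes, replace the participant random intercept by an unstructured within-participant covariance over the three visits, fitted by REML with Kenward-Roger degrees of freedom. State that time is categorical and that the primary test is the group contrast at 4 months. This is valid whichever covariance pattern holds.

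Cost: one changed model statement. Three visits need six covariance parameters (three variances, three covariances) instead of two, which is easily supported by 192 participants, or about 163 at 15% loss (192 × 0.85 = 163.2). The confidence interval may be slightly wider. The article expects recruitment to run to June 2028 and plans no interim analysis, so the change can be made before outcome data are compared by arm.

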#### Secondary comparative analyses

Aim 2/Hypothesis 2: *Compared to control, participants assigned to integrated nocturia and insomnia behavioral intervention will have greater reduction in self-reported wake after sleep onset and Insomnia Severity Index over the 4-month follow-up period*. Secondary outcomes, patient-reported wake after sleep onset and ISI, will be modeled similarly with a (G)LMM in the original scale or transformed scale as appropriate, where group, time, time*group interaction, and stratified randomization variables (study site and sex) will be included in fixed effects, and random effects will be included for nested clustering by site and participant to account for correlations due to clustering. If the distributions of the secondary outcomes are skewed and no good transformation is found, the outcomes will be categorized into categories based on quantiles or clinically meaningful values and then modeled with GLMMs using cumulative logit or generalized logit link for multinomial data. Similar fixed and random effects will be included in GLMMs. Due to the exploratory feature, no adjustment will be made for the multiple comparisons, but results will be presented as secondary outcome analyses. Secondary analyses similar to those proposed in Aim 1 will be performed on the secondary outcomes of patient-reported wake after sleep onset and ISI.

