### Objectives {7}

#### Specific Aim 1

Determine the efficacy of the integrated nocturia and insomnia behavioral intervention program for improving nocturia frequency over 4 months in older adults with nocturia and insomnia symptoms.

##### Hypothesis 1

Compared to a control arm of health education, participants assigned to the integrated intervention program will demonstrate a greater reduction in mean nocturia frequency over 4 months.

#### Specific Aim 2

Assess the efficacy of the integrated nocturia and insomnia behavioral intervention for reducing sleep disturbance over 4 months in older adults with nocturia and insomnia symptoms.

##### Hypothesis 2

Compared to a health education control arm, participants assigned to the integrated intervention program will have greater reduction (i.e., improvement) in self-reported wake after sleep onset and Insomnia Severity Index over the 4-month follow-up period.

#### Specific Aim 3

Examine the effects of the integrated nocturia and insomnia behavioral intervention on quality of life (daytime function) related to nocturia and sleep quality over 4 months in older adults with nocturia and insomnia symptoms.

##### Hypothesis 3

Participants randomized to the integrated intervention program will report more improvement in Nocturia-Quality of Life scores and Pittsburgh Sleep Quality Index Global Score (lower scores) from baseline to post-treatment and 4-month follow-up compared to control.

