#### Secondary outcome: diary-assessed maintenance insomnia

Specific measurement variable: Wake after sleep onset is derived from the 7-day Sleep/Bladder Assessment Diary for diaries with ≥ 5 days of data. The sleep diary items are adapted from American Academy of Sleep Medicine Consensus Sleep Diary [48] for daily sleep schedule, habits, and medication use. A difference of 20 min between treatment and control is considered the clinical significance threshold for studies of chronic insomnia disorder [49].Analysis metric: wake after sleep onset (4 months post-randomization)Method of aggregation: meanTime point: 4 months post-randomization

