#### Secondary outcome: insomnia severity

Specific measurement variable: Insomnia Severity Index (ISI) [50] total score is based on a 7-item instrument with high internal consistency (Cronbach alpha 0.9) and high convergent validity for measures of fatigue, quality of life, anxiety, and depression [51]. The total score measures perceived severity of insomnia symptoms. A 0.5 standardized mean difference between treatment and control is considered the clinical significance threshold for studies of chronic insomnia disorder [49].Analysis metric: Insomnia Severity Index (4 months post-randomization)Method of aggregation: meanTime point: 4 months post-randomization

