### Sample size {14}

Power calculations are informed by parameter assumptions derived from past clinical trials of behavioral interventions for lower urinary tract symptoms and/or sleep disorders conducted by our study team members or consultants, corroborated by trends in our previous integrated nocturia and insomnia intervention feasibility study [36, 37, 55]. We assume an average frequency of at least 16 nocturia episodes per week (~ 2.3 episodes/night) in our baseline trial population, and an average decrease in nocturia frequency of 2 episodes per week (~ 0.3 episodes/night) over 4 months in the control group, given a recent systematic review including 17 trials assessing placebo-response in studies of treatments for nocturia [56]. We also anticipate a clinically meaningful reduction in nocturia frequency (item from the ICIQ-OAB) in the integrated nocturia and insomnia intervention group of at least 7 episodes per week (~ 1 episode per night) over 4 months, leading to a between-group difference in improvement in nocturia frequency of 5 or more episodes per week (0.7 episodes/night) between the integrated nocturia and insomnia intervention and control arms. This effect size represents a meaningful threshold of improvement in nocturia frequency that can be communicated to patients and clinicians, and corresponds to a clinically meaningful improvement of greater than half a standard deviation in the mean nightly nocturia frequency given a range of potential standard deviations [56, 57]. Using an approximation of the covariance matrix of the regression coefficients of the proposed linear mixed effects models (LMMs), we estimate that a sample of 192 participants, randomized in equal proportions to the two arms, will provide > 80% power in 2-sided tests with an experiment-wise type-I error rate of 5% [58], to detect the proposed greater reduction in nocturia frequency of least 5 episodes/week (0.7 episodes/night) associated with integrated intervention versus control intervention, assuming a cumulative loss to follow-up level of less than 15% accumulated at roughly equal rates between sequential follow-up visits. The assumption of loss-to-follow-up < 15% is based on our existing integrated intervention feasibility study, as well as prior trials of behavioral treatment programs for urologic symptoms conducted by the investigators in which early termination was < 15% over similar time periods [36, 37].

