### Methods for additional analyses (e.g., subgroup analyses) {20b}

ICIQ-Nqol scores and PSQI Global scores will be modeled similarly with (G)LMMs in their original scale or transformed scale as appropriate, with similar fixed effects and random effects as proposed in Aims 1 and 2. If the distributions of the ICIQ-Nqol and PSQI Global scores are skewed and no good transformation is found, the outcomes will be categorized into categories based on quantiles or clinically meaningful values and then modeled with GLMMs using cumulative logit or generalized logit link for multinomial data. Similar fixed and random effects will be included in GLMMs. Due to the exploratory feature, no adjustment will be made for the multiple comparisons, but results will be presented as secondary outcome analyses. Similar secondary analyses as those proposed in Aim 1 will be performed on the secondary outcomes ICIQ-Nqol and PSQI.

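### If skewed secondary outcomes reach the categorization fallback, cutting them and allowing a generalized logit discards information, and the odds ratios cannot be read against the plan's mean-based benchmarks

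*Protocol article*

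**What the plan says.** Under Secondary comparative analyses, WASO and ISI are first modelled on the original or a transformed scale. The text then provides for distributions that are "skewed and no good transformation is found, the outcomes will be categorized into categories based on quantiles or clinically meaningful values", after which they are "modeled with GLMMs using cumulative logit or generalized logit link for multinomial data". The section on additional analyses {20b} repeats the fallback for the exploratory scores: "If the distributions of the ICIQ-Nqol and PSQI Global scores are skewed and no good transformation is found".

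The outcome definitions are on a mean scale. The Abstract gives WASO in mean minutes, and the Outcomes section aggregates both WASO and ISI as means at 4 months. For WASO it adds: "A difference of 20 min between treatment and control is considered the clinical significance threshold". For ISI: "A 0.5 standardized mean difference between treatment and control is considered the clinical significance threshold". Hypothesis 2 in Objectives {7} is framed as a "greater reduction (i.e., improvement) in self-reported wake after sleep onset and Insomnia Severity Index over the 4-month follow-up period".

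The article does not say that a mean difference would still be reported if the fallback is used.

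**The concern.** Three features of the fallback work against the trial.

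- **Cutting is unnecessary.** A cumulative-logit model needs only ordered values. It can be fitted to WASO minutes or ISI points as they stand, so grouping discards information for no gain.
- **The generalized logit treats the groups as unordered.** Minutes and scores are ordered. That model spends one degree of freedom per non-reference group on what is essentially a one-directional question.
- **The result changes scale.** An odds ratio across groups is not a difference in minutes or a standardized mean difference. If the fallback is used and nothing else is reported, Aim 2 is answered on a scale that the plan's own benchmarks cannot interpret.

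At stake are the precision and readability of the Aim 2 results and of the exploratory quality-of-life and sleep-quality results.

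**Working it through.** **Inputs from the article.** Sample size {14} gives "a sample of 192 participants, randomized in equal proportions to the two arms", so 96 per arm, with loss below 15%: 96 × 0.85 = 81.6 per arm, or about 163 in total. Tests are two-sided at 5%. The benchmarks are 20 minutes (WASO) and 0.5 SMD (ISI).

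**Inputs assumed.** The article gives no SD or distribution for WASO or ISI, so several shapes were tried.

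**The plan's own power figure.** It concerns the primary outcome only: more than 80% for 0.7 episodes per night. The statement that this exceeds half an SD implies SD < 0.7 / 0.5 = 1.4. With 81.6 per arm, power is 89% at SD 1.4 and reaches 80% at SD of about 1.60. The figure is consistent, though not exactly reproducible without an SD. No power is stated for the secondary outcomes. At an SMD of 0.5, a mean comparison has Φ(0.5 × √(81.6/2) − 1.96) = Φ(3.19 − 1.96) = 89%.

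**Step 1: the cost of cutting.** Under proportional odds, k equal groups have efficiency 1 − 1/k² relative to the uncut ordinal analysis:
- k = 2: 1 − 1/4 = 75%, as if 163 participants were 122
- k = 3: 1 − 1/9 = 89%, as if 145
- k = 4: 1 − 1/16 = 94%, as if 153
- k = 5: 1 − 1/25 = 96%

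**Step 2: the cost of ignoring order.** A 1-df test with 80% power has noncentrality (1.960 + 0.842)² = 7.85. If the same signal is spread over 2 df (three groups), power is 71%. Over 3 df (four groups) it is 64%.

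**Step 3: simulation.** There were 82 per arm and 4,000 runs per shape, in a cross-sectional approximation at 4 months. A Welch test stands for the mean difference, a Wilcoxon test on uncut or grouped values for the cumulative logit, and a chi-square test for the generalized logit. Power in %:

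| Shape (assumed) | Mean difference | Uncut ordinal | Cumulative logit, 2/3/4/5 groups | Generalized logit, 2/3/4/5 groups |
|---|---|---|---|---|
| Normal, SMD 0.5 | 89 | 87 | 70/80/83/86 | 70/74/71/67 |
| Gamma, 70 vs 50 min, equal CV | 85 | 79 | 58/69/72/77 | 58/64/60/57 |
| Gamma, 70 vs 50 min, SD 45 in both arms | 81 | 95 | 82/91/92/94 | 82/89/89/87 |
| Log-normal, 70 vs 50 min, equal CV | 87 | 90 | 74/84/86/90 | 74/79/76/72 |
| Effect in upper tail only, mean difference 20 min | 97 | 36 | 10/17/21/29 | 10/23/39/54 |

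In every shape, cumulative logit on groups had less power than the uncut ordinal test, clearly so with 2 groups and only slightly with 5. The generalized logit was usually worse still. The exception is the tail-only shape, where 4 or 5 unordered groups beat the uncut ordinal test but stayed far below the mean comparison.

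**Step 4: does skew break the mean comparison?** Under a null with strong skew (gamma, mean 60, SD 50), its type I error was 4.9%. A mean difference can therefore be reported beside the fallback model without losing the 5% level at this sample size.

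**The case against.** The strongest reply is that the fallback may never be used. It needs skew and also the failure of every sensible transformation. Log-normal WASO would be handled by a log transformation: with log-SD 0.8 and a 30% reduction (assumed), the log-scale comparison has 81% power, and the plan would stop there. A reader might infer that right-skewed minutes make the fallback likely. The article gives no WASO distribution, so that does not follow.

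A reader might also infer that grouping loses power against an ordinary linear model. That is not generally true. In the same log-normal setting, the raw linear comparison has 69%, while cumulative logit on 3, 4 and 5 groups has 74%, 74% and 77%. The gamma shape with equal SDs points the same way. The reliable loss is against the uncut ordinal analysis.

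Nor does the article say that cut-points, number of groups or link will be picked after seeing the data. Clinically meaningful cut-points can be fixed in advance, and such detail commonly sits in an analysis plan that is not shown. Its absence here is no fault.

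Finally, the two benchmarks are interpretive. The article ties no decision rule to them, and nothing forbids reporting arm means beside the fallback model. All of this stands, and it limits the point. It does not remove the stated commitment to cut ordered values, the stated option of an unordered link, or the mismatch of scale.

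**Conclusion.** The point holds as a limited improvement to a conditional analysis. The primary analysis has no such fallback and is unaffected.

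The efficiency figures in Step 1 assume proportional odds and equal-sized groups, and the 71% and 64% assume that the signal is unchanged as degrees of freedom are added. The simulated powers rest on assumed distributions and ignore the planned repeated-measures structure, so they show direction and rough size only.

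The scale mismatch needs no such assumption: an odds ratio cannot be compared with 20 minutes or with an SMD of 0.5.

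The evidence does not support making the raw-scale linear model the estimate in all cases. That would displace the planned transformed-scale analysis, which can be more powerful, and the choice between them is a trade-off. The tail-only shape shows why the mean difference should accompany any ordinal fallback: the uncut ordinal test had 36% power where the mean comparison had 97%.

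**What to change.** In Secondary comparative analyses:
- Keep the original-scale or transformed-scale linear mixed model as planned.
- Replace the categorization fallback with a cumulative-logit mixed model on the uncategorized, ordered values, with the same fixed and random effects.
- Remove the generalized logit option.
- State that whenever the fallback is used, the between-arm mean difference at 4 months is also reported, in minutes for WASO and in points and standardized form for ISI, with robust or bootstrap standard errors, and is read against the 20-minute and 0.5-SMD benchmarks.

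Make the same change in the section on additional analyses {20b} for ICIQ-Nqol and PSQI, reporting the mean difference in scale points.

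The cost is wording, a little more analysis work, and possibly a slightly wider interval for the mean difference. The article expects recruitment to run to June 2028, so the change can be made before any analysis.
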